### Data collection, management, and monitoring

In each case, a number of characteristics related to the mother, delivery, and newborn will be recorded (Table 4). These data will be inserted a posteriori in the electronic case report form created for the study and will be accessible for those responsible for the study in the coordinating center. The recorded information corresponding to the SO_2_ and HR for each case will be electronically downloaded through various report formats, which in turn will be submitted to the coordinating center by e-mail. The coordinating center has the appropriate software for reading and analyzing the recorded pulse oximetry data.

**Table 4 Tab4:** Demographic data to be recorded in each case

- *Mother-related*: age, country of origin, medical history of interest, parity, desire to breastfeed, increase in weight during pregnancy, body mass index, bra size (including cup size), a history of children who died, and medication consumed during the 72 h prior to delivery	
- *Delivery-related*: date and time, duration, time of completion, spontaneous or induced, delivery position, epidural anesthesia, time of epidural, time the water broke, nuchal cord, episiotomy, artery and umbilical vein blood gas test, maternal medication during labor and 2 h afterwards.	
- *Neonate-related*: sex, weight, gestational age, Apgar score, cord pH, presence of crying at birth, and time of the first breast latch	

The implementation of post-randomization exclusion criteria will be evaluated in a reliability study. Two investigators will independently assess the criteria in a sub-sample of study participants. Reliability and agreement statistics will be reported.

### Statistical methods

As we estimate a relevant proportion of estimated postrandomization exclusions, we will perform a modified intention to treat analysis.

The study will employ a two-tailed significance level of 5%. The confidence intervals will be 95%. The main assessment criterion is the presence of an episode of SO_2_ ≤ 90%. We will perform an unadjusted analysis of the intervention’s effect with chi-squared test.

The distribution of the baseline prognostic variables will be analyzed with the mean and standard deviation for the continuous variables (we expect a normal distribution) and with numerators/denominators and percentages for the categorical variables. *P* values will not be included, but we will indicate the variables that have a strong association that could have a confounding effect—even if the distributions in the two study groups are not very different—and the variables with large differences between the groups that could have a confounding effect, even those with a poor association. Stratified analysis and logistic regression modeling will be performed on the primary outcome to take into account covariates (i.e., exploring the possible effect of modification of breast feeding, adjusting for relevant covariates, etc.). The strategies for missing-data imputation and the subgroup analysis will be documented a priori.

The statistical analysis will be conducted using the software environment R [28].

An independent committee, which will include an independent biostatistician, will review the results of the interim analysis.

The study will be halted if differences in the main outcome show a *p* value below 0.001 to protect the overall type I error of the trial. The study will also be interrupted on safety grounds due to any other results that show a negative effect on the child or mother considered relevant by the committee.

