## Methods

### Study setting

This study emerged from the research group setting of the Spanish Collaborative Research Network for Maternal and Child Health (SAMID Network; reference RD12/0026/0007) and is financed by the Carlos III Health Institute of Spain. Ten Spanish hospitals from various regions and healthcare levels are participating in the study, which together cover approximately 27,000 births a year. The coordinating center is Hospital 12 de Octubre of Madrid. The research groups involved in the study have experience in participating and coordinating relevant European and international projects.

These hospitals have beds with adjustable tilt for the women. Each of the centers is equipped with a remote SO_2_ and HR monitoring system (Masimo Patient SafetyNet®) for the newborns and have computer systems that provide 24-h access to the study’s computer platform to conduct the randomization and data entry into the electronic notebook. The mean number of researchers per center is 10, with a range of 2–20.

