### Allocation and blinding

The randomization was conducted using permuted blocks. To this end, we employed a shared computer platform. Each center was assigned a block, and the patients were randomized one after another according to the random numbers contained in the corresponding block. Each center’s block size was created after an initial calculation of the number of mother/newborn dyads the center could recruit over the course of a month (the block sizes ranged from 193 to 1076 cases). The patients will be randomized at the start of labor. Once the informed consent form is signed, the researcher who obtained the consent will access the shared computer platform with the center’s specific login. The platform will then take the researcher directly to their block of random numbers and show them the mother’s degree of inclination. Beforehand, the researcher must answer a series of questions to confirm that the dyad meets all study inclusion criteria and none of the exclusion criteria. The center’s researcher is not allowed to know the block of numbers they are given nor the sequence of numbers. The recorded pulse oximetry data (SO_2_ and HR) will be extracted and analyzed in the coordinating center by researchers who will be blinded to the mother’s sitting angle in bed.

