The study is multicenter, which could entail certain variability in a number of the study procedures despite previous agreements, which could represent a limitation. Thus, in the hospitals in which the delivery and postpartum take place in different rooms, the pulse oximeter will be disconnected while the mother and child are transferred, and there will be a loss of data during this time interval. The SSC procedure itself or the method for achieving proper bed inclination might not be uniform. Lastly, the clinical practice of the various centers regarding the clamping of the umbilical cord (early or late clamping, umbilical cord milking) varies. Another limitation consists of the fact that the study will not have the services of a contract research organization (CRO). The coordinating center’s researchers will be responsible for monitoring the proper application of the study protocol.

The study results may not be applicable to newborn groups with different characteristics but who are still candidates for SSC (late-preterm newborns, newborns with disease during the pregnancy, and/or delivery that does not contraindicate SSC).

One of the study risks is that it can lead to the monitoring of all newborns during their time in SSC and potentially to separating many newborns from their mothers. This is not the study’s objective, which seeks only to observe the effect of the bed position.

The study is focused on analyzing what occurs during the first 2 h after delivery. It would be interesting to extend the analysis time to the first 24 h of life while the mother and child are in SSC. It would also be important to determine whether the degree of inclination could influence the mother’s recovery and state of health during the immediate postpartum.

Even if the results of this study can shed some light on our understanding of these events, they will not preclude medical personnel from continuing to give mothers and their companions the recommendations that various experts have indicated in terms of safely implementing SSC [12, 13, 15, 16, 20–22, 24, 27, 29, 38, 39].

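### Allocation is generated separately in each center, but the stated primary test is an unadjusted chi-squared test that ignores center; the test stays valid, and stratifying it would be a small, nearly free gain.

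*Protocol article*

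**What the plan says.** **Allocation.** Under Allocation and blinding: "Each center was assigned a block, and the patients were randomized one after another according to the random numbers contained in the corresponding block". The same section adds that "the block sizes ranged from 193 to 1076 cases". Under Study setting: "Ten Spanish hospitals from various regions and healthcare levels are participating in the study". Randomization is therefore stratified by center.

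**Primary analysis.** Under Statistical methods, the test for an episode of SO2 at or below 90% is fixed: "We will perform an unadjusted analysis of the intervention’s effect with chi-squared test". Stratified and logistic analyses of the same outcome follow, to take covariates into account, but center is not named in them.

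**Center differences.** The Discussion lists as a limitation: "The study is multicenter, which could entail certain variability in a number of the study procedures despite previous agreements". Its examples are recordings interrupted by transfer between rooms, the way skin-to-skin contact is carried out, how the bed angle is achieved, and cord clamping.

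**Flagging of confounders.** Statistical methods gives two routes. The first rests on association with outcome: "we will indicate the variables that have a strong association that could have a confounding effect—even if the distributions in the two study groups" are similar. The second rests on imbalance: "the variables with large differences between the groups that could have a confounding effect, even those with a poor association".

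**The concern.** An analysis normally reflects the factors used to restrict the randomization. Here the restriction is by center, and the article itself gives reasons why the event rate could vary by center. For example, a hospital that disconnects the oximeter during transfer records less time in which an episode can be seen. When the strata predict the outcome and the arms are roughly balanced within them, a pooled test leaves between-center variation in its error term. Its standard error is then somewhat too large and some power is lost. The trial already holds the information needed to recover that power.

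The secondary issue is the imbalance route. A large chance difference between arms in a variable that hardly predicts the outcome is a poor reason to adjust for it. If that list fed the adjusted model, the content of the model would depend on the observed data.

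**Working it through.** **1. The plan's own figure.** Inputs from Sample size and recruitment: 9% v 6%, two-sided 5%, power 80%.

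- Uncorrected n per group = [1.960·√(2·0.075·0.925) + 0.842·√(0.09·0.91 + 0.06·0.94)]² / 0.03² ≈ 1209.
- Continuity-corrected n = (1209/4)·[1 + √(1 + 4/(1209·0.03))]² ≈ 1275, which is the stated figure.
- 2 × 1275 = 2550; 2550/0.5 = 5100; 5100 × 1.15 = 5865, against 5866 stated.

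The calculation has no center term and needs none.

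**2. Upper bound on the excess variance.** With exact balance within centers, the pooled variance is too large by about Var(p_c)/[p(1−p)]. With p = 0.075, p(1−p) = 0.0694.

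- Center SD 2 points: 0.0004/0.0694 = 0.6%.
- Center SD 3 points: 0.0009/0.0694 = 1.3%.
- Center SD 5 points: 0.0025/0.0694 = 3.6%.

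Exclusion after randomization shrinks this. Take a block of N split equally, with each dyad kept with probability 1/2. The difference in arm sizes then has variance N/4, against N/2 under simple randomization of the same number kept. The excess is roughly halved.

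**3. Simulation.** There were 40,000 trials per setting, with ten centers, 1:1 allocation within center and 50% random exclusion. The common odds ratio was (0.06/0.94)/(0.09/0.91) = 0.645. Two inputs are assumptions. The individual block sizes were set between 193 and 1076 and sum to 5866; the article gives only the range. The between-center SD of the log-odds was varied from 0 to 1.0; the article gives none. Type I error was run at 5866 randomized, and power at about 2550 evaluable.

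| Center SD (logit) | Type I, chi-squared | Type I, CMH | Power, chi-squared | Power, CMH | Gain (points, unrounded inputs) |
|---|---|---|---|---|---|
| 0 | 5.0% | 5.0% | 82.3% | 82.2% | −0.1 |
| 0.3 | 4.9% | 4.9% | 81.4% | 81.5% | 0.1 |
| 0.5 | 4.9% | 5.0% | 80.7% | 80.9% | 0.3 |
| 0.8 | 4.6% | 5.0% | 77.6% | 78.8% | 1.2 |
| 1.0 | 4.6% | 5.0% | 74.4% | 76.2% | 1.8 |

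Power falls with SD for both tests, so only the gap between them bears on this point. At 5866 randomized the power figures are 85.6% v 85.9% (SD 0.5) and 79.8% v 81.6% (SD 1.0). A separate run with exact balance within centers in the analyzed set gave a chi-squared type I error of 4.2% at SD 1.0. That is more conservative, in line with step 2.

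**4. Feasibility of stratifying.** The smallest block, 193, leaves about 96 evaluable newborns and 96 × 0.075 ≈ 7 events. The whole trial expects 2550 × 0.075 ≈ 191 events. Ten strata, or nine center terms, are easily supported.

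**5. The covariate text.** The two routes stand in the sentence on presenting baseline variables, and the verb there is to indicate. The regression comes in the next sentence, which speaks only of relevant covariates. The article does not say that the flagged variables enter the model.

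**The case against.** The strongest reply is that an unadjusted test fixed in advance is a defensible primary analysis. It is simple, its error rate does not exceed 5%, and the gain from stratifying is below one point unless centers differ a great deal, a quantity the article does not give. All of this stands, and it limits the point to an improvement in efficiency.

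A reader might infer that the pooled test is biased because the half of dyads lost after randomization unbalances the arms within centers, so that center differences mix into the angle effect. The documents do not support this. If exclusion is unrelated to arm, that imbalance is chance, which the pooled standard error already covers; the simulation includes the 50% loss and shows no inflation. If exclusion did depend on arm within a center, stratifying by center would not cure it.

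A reader might also infer that the adjusted model draws its covariates from observed imbalance and so has misstated error rates. The article says only that such variables will be indicated, and its other route is association regardless of imbalance. Nothing calculated here measures an effect on error rates, and the adjusted model is not the primary test. The exact covariate list may be in an analysis plan that is not shown, so its absence is no finding.

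**Conclusion.** The point holds as a mismatch between design and primary analysis, with a small cost and no consequence for validity. The pooled chi-squared test has type I error of about 4.6% to 5.0%. It gives up about 0 to 2 points of power over an assumed center SD of 0 to 1.0 on the logit scale, and about 0.5 point or less up to SD 0.5. These figures rest on assumed center SDs and block sizes, a common odds ratio, and exclusion unrelated to arm. The sample size stands.

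On covariates, what remains is minor: flagging by between-group difference, even for weakly prognostic variables, is harmless as description but should not become a rule for choosing the adjusted model.

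**What to change.** In Statistical methods, name as primary a Mantel-Haenszel risk difference (with risk ratio) stratified by center and its CMH test, and keep the unadjusted chi-squared as supportive. Logistic regression with center is an acceptable alternative, but it gives a conditional odds ratio, whereas the objective and sample size are framed as proportions. State that the interim p value comes from the same test.

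For the adjusted analysis, fix a short list in advance: center plus prognostic variables from Table 4 known before the bed angle is set, such as parity, gestational age and epidural. Items arising later, such as time of first latch or maternal medication in the 2 h after delivery, do not belong in it. State that observed differences between arms play no part in the choice.

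The cost is wording only. Center and the Table 4 variables are already collected, and no further participants are needed. The change should be made before unblinded outcome data are seen.

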**Methods:**

The study participants will be full-term healthy mother–newborn dyads from ten hospitals in Spain. Participants will be randomly assigned to one of two study arms defined by mother’s bed inclination (45° or 15°). The planned sample size is 5866. Centralized permuted blocks randomization and assessor blinding will be implemented.

The newborns will be monitored remotely with pulse oximetry, from 10 min to 2 h after delivery. We established SO_2_ and heart rate (HR) limit alarms, as well as an action protocol in the event of alarm activation.

The primary outcome is the number of healthy newborns who undergo episodes of SO_2_ ≤ 90%. Secondary outcomes are the mean SO_2_ level, the number of newborns who experience episodes of SO_2_ ≤ 85%, the time to SSC discontinuation due to abnormal SO_2_ or HR, and episodes of HR < 111 beats per minute (bpm) or > 180 bpm. Subgroups and pooled analysis will be performed to identify if breast-feeding and mother and child positions favor the occurrence of desaturation or bradycardia episodes.

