### Interventions

Before starting patient enrollment, all participating centers have agreed upon the SSC procedure and the study intervention. Additionally, the coordinating center has conducted face-to-face training sessions in each of the hospitals.

When a possible case is identified, consent from the pregnant woman will be requested. Once the woman has agreed to participate, she is shown a number of photographs of how to perform SSC (Fig. 1; “Models for mother’s and newborn’s positions for 15° and 45° inclination”). The woman is told to record the moment(s) when the newborn latches on to the breast. The woman’s data are subsequently entered into the computer platform to proceed with the randomization. After the delivery, the researcher attending the birth will verify that the case does not meet any of the postrandomization withdrawal criteria. The pulse oximetry apparatus (noninvasive Radical-7 Signal Extraction PulseCO-Oximeter® monitor equipped with Masimo Rainbow SET® technology) is then plugged into the power outlet and to the data collection and is subsequently turned on. The pulse oximeter alarms have been established at 91% as the lower limit for SO_2_; the upper limit has not been set. For the HR, the lower limit alarm has been set to 111 bpm and the upper limit to 180 bpm.

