**Fig. 4 Fig4:**
[figure not shown]
Action protocol when a HR > 180 or < 111 bpm clinical alarm sounds

If the CE cannot be explained by any of the above causes, the CE will be considered a CRE depending on whether it occurs for the first or second time, the magnitude of the desaturation, additional heart rate impairment, or if the newborn is symptomatic. A CRE entails the termination of the intervention.

Investigators at the coordinating center will review the compliance with the intervention protocols. If noncompliance is detected, the head of each participating center will be contacted, and the deviations from the protocol will be discussed.

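### Breastfeeding during SSC is to be related to a yes/no episode outcome, although an episode that ends SSC prevents later latching, so breastfeeding can falsely look protective

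*Protocol article*

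**What the plan says.** Under Allocation and blinding: "The patients will be randomized at the start of labor". The abstract sets the outcome window: "The newborns will be monitored remotely with pulse oximetry, from 10 min to 2 h after delivery". Under Statistical methods the outcome is binary, "The main assessment criterion is the presence of an episode of SO"₂ ≤ 90%, and the primary test leaves breastfeeding out: "We will perform an unadjusted analysis of the intervention’s effect with chi-squared test".

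The same section then names stratified analysis and logistic regression on that primary outcome, with this example of their use: "exploring the possible effect of modification of breast feeding, adjusting for relevant covariates". The abstract states the aim more broadly: "Subgroups and pooled analysis will be performed to identify if breast-feeding and mother and child positions favor the occurrence of desaturation or bradycardia episodes". The Discussion makes clear that the breastfeeding of interest is breastfeeding during SSC.

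Timing data are collected. Under Interventions: "The woman is told to record the moment(s) when the newborn latches on to the breast". Table 4 lists the time of the first latch and, separately, the mother's desire to breastfeed.

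On stopping, the action protocol for alarms says: "A CRE entails the termination of the intervention". Events judged not clinically relevant do not end the intervention.

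**The concern.** Breastfeeding during SSC is not a baseline characteristic. It begins after randomization, within the interval in which episodes are counted, and it can occur only while SSC continues. Two errors follow when it is entered as a yes/no factor against a yes/no outcome.

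- A newborn whose first episode ends SSC before any latch can no longer latch in SSC and falls into the not-breastfed group because of the episode.
- A newborn who has an episode, stays in SSC and latches afterwards is counted as a breastfed newborn with an episode, although the episode came first.

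The first error makes breastfeeding look protective. That matters because the Background lists breastfeeding among the suspected contributors, through airway obstruction and vagal tone. The error therefore runs toward false reassurance on a question the trial says it will address.

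**Working it through.** **The plan's own figure.** The article gives no figure for the breastfeeding analysis. Its sample size, 1275 per group for 9% vs 6% with two-sided 5% and 80% power, reproduces exactly with the continuity-corrected two-proportion formula (1209 without the correction). Nothing below changes it.

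**Inputs from the article.** Window T = 120 − 10 = 110 min. Episode risk p = 7.5%, the midpoint of 9% and 6%.

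**Assumptions (not in the article).** Latching has no effect on episodes; the episode hazard is constant; latch time is exponential with median m minutes after recording starts (m = 50 is 60 min after birth; m = 30 is 40 min); a share f of first episodes ends SSC.

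**Formulas.**
- λ = −ln(1 − p)/T; μ = ln 2/m
- Chance of latching in an undisturbed window: L = 1 − 2^(−T/m)
- Chance that the latch comes before the episode, given an episode: A = 1 − [λ/(λ+μ)]·[1 − e^(−(λ+μ)T)]/p
- Share of newborns with an episode who count as latched: s = (1 − f)L + fA
- Ever-latched odds ratio = [s/(1 − s)] / [L/(1 − L)]

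**Numbers for m = 50, f = 20%.** λ = 0.000709, μ = 0.01386, L = 0.782, A = 0.482. Then s = 0.8 × 0.782 + 0.2 × 0.482 = 0.722. Odds ratio = (0.722/0.278)/(0.782/0.218) = 2.60/3.59 = 0.72. As risks: 7.0% in latched and 9.4% in never-latched newborns, where the truth is 7.5% in both. For m = 30, L = 0.921 and A = 0.632.

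| f | m = 50, formula | m = 50, simulated | m = 30, formula | m = 30, simulated |
|---|---|---|---|---|
| 0% | 1.00 | 1.0 | 1.00 | 1.0 |
| 5% | 0.92 | 0.91 | 0.83 | 0.84 |
| 10% | 0.845 | 0.84 | 0.71 | 0.71 |
| 20% | 0.72 | 0.73 | 0.54 | 0.55 |
| 50% | 0.48 | 0.48 | 0.30 | 0.30 |

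The simulated columns (4 million newborns) agree within 0.01. A slower latch weakens the bias: with a median of 90 min after birth and arms at 9% and 6%, simulation gives 0.89, 0.76 and 0.59 at f = 10%, 25% and 50%.

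**Time-split check.** In simulations with the same constant hazard, counting first episodes per person-time before and after first latch gives a rate ratio of 0.99 to 1.01 in every scenario.

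**Lost time order.** With a true doubling of hazard after first latch, the simulated ever-latched odds ratio is 1.66–1.74 at f = 0, 0.97–1.25 at 20% and 0.55–0.87 at 50%. The time-split rate ratio stays at 2.0.

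**Effect of angle by stratum.** The overall arm odds ratio is (0.06/0.94)/(0.09/0.91) = 0.645. If latching is the same in both arms, L cancels: the latched stratum gives 0.645 × s₄₅/s₁₅ and the other 0.645 × (1 − s₄₅)/(1 − s₁₅). With m = 50 and f = 20% in both arms, s is 0.722 and 0.723, and the strata give 0.646 and 0.644. With f = 20% at 15° and 10% at 45°, s₁₅ = 0.722 and s₄₅ = 0.752. The strata then give 0.645 × 1.042 = 0.67 (latched) and 0.645 × 0.891 = 0.57 (not latched).

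**A trap in the remedy.** Time after latch is also later time. If the episode hazard halves every 60 min (assumed) and latching has no effect, a before/after rate ratio without time since birth is 0.72 at m = 50.

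**The case against.** The strongest reply is that the article says the subgroup analysis will be documented a priori, never defines breastfeeding as ever latched, and collects latch moments, so a later plan may handle timing properly. That is fair on definitions, and ever-latched is the coding assumed here. It does not remove the point: the method the article names is stratification and logistic regression on a yes/no outcome, which by itself cannot order latch and episode.

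The size is also open. Only clinically relevant events end SSC; those explained by crying, movement, handling or poor signal do not. The share could be small, and at 5% with a median latch 50 min into the recording the bias is mild.

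Three stronger readings are tempting, and the documents do not support them.

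- *The primary result is biased.* It is not; the chi-squared test ignores breastfeeding.
- *The plan will report false modification of the angle effect.* This does not follow from the mechanism alone: with equal latching and termination by arm, the strata agree. It needs angle to change one of them. The article does not rule this out, since SSC interruption is itself compared between arms, but it does not show it either.
- *The arm effect will be adjusted for latching.* The sentence lists breastfeeding as a possible effect modifier and relevant covariates as a separate item; it does not say that latching is one of them.

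**Conclusion.** The concern holds for the association between breastfeeding during SSC and episodes. The stated binary analysis lets the outcome determine the exposure and discards the order of events. With no true effect, the ever-latched odds ratio runs from 1.00 down to 0.48 (median latch 50 min into the recording) or 0.30 (30 min) as the share of first episodes ending SSC goes from 0% to 50%. This false signal is always toward protection. The size rests on assumed latch times and an assumed termination share. The analysis is secondary and exploratory, so this should be changed but does not threaten the trial's main conclusion.

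**What to change.** Under Statistical methods, replace the binary breastfeeding analysis of episodes with a Cox model for time to first episode on the time-since-birth scale. Enter first latch as a time-dependent exposure with an arm-by-latch term, and censor at the end of SSC or of recording. If a Poisson model is preferred, include time-since-birth intervals.

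Report the result as risk after first latch, not risk during a feed: Table 4 lists only the first latch, and the article does not mention recording the end of a feed.

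For subgroup analysis of the angle effect, use the recorded desire to breastfeed, and state that it reflects the mother's intention before delivery, because case data are entered afterwards.

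The cost is wording and some programming. Latch times and recordings stored every 2 s already exist, and the sample size and primary test stay as they are. The estimate remains exploratory and non-randomized: newborns who latch early may differ in other ways.
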